### Collaborative teams

#### Steering committee

A group of medical students whose role is to design the protocol, final dataset handling and analysis and drafting of the paper.

#### Mini-teams

Mini-teams consist of five collaborators at each site whose role is to identify eligible patients receiving appendicectomies during the study periods and collect data. The mini-teams are planned to consist mainly of student data collectors who are currently on placement at the relevant hospital, recruited through the student research network STRIVE WA. One collaborator is to be selected as the local lead. For every center, there is to be a local lead in the form of a surgical consultant, who coordinates and supervises the actions of that center. All collaborators part of a mini-team whose data is accepted for the final pooled analysis will be listed as co-authors on the final manuscript.

### Sample size

There are over 1600 participants that are planned to be included. This estimate was obtained from the Australian Government Medical Statistics Record, which displayed 818 WA claims for MBS item number 30720, the code for the surgical operation to be examined within this study from July 2022 to June 2023. Assuming this is representative for the beginning of 2022 to the end of 2023, the study window for this project, the number of participants can reasonably be estimated to be double this figure.

Amongst the metropolitan hospitals (Royal Perth Hospital, Sir Charles Gairdner Hospital, Fiona Stanley Hospital and Armadale Health Service), there will be 350 participants each, and at the rural hospitals (Albany Hospital, Bunbury Hospital, Broome Health Campus, Geraldton Hospital and Hedland Health Campus), there will be 50 participants each. This is reflective of the respective sizes of the hospitals.

### Data collection and storage

Data will be collected and stored online through a secure server running the Research Electronic Data Capture (REDCap) web application. REDCap allows collaborators to enter and store data in a secure system. Collaborators will be given individual REDCap login details, allowing secure data storage on the REDCap system. No identifiable patient information will be collected. Collaborators may wish to first record data on a paper version of the data collection pro-forma. Paper copies of any data should be destroyed as confidential waste within the center once uploaded to REDCap.

Identifiable patient information will not be entered into REDCap since only the case report forms will be completed for every eligible instance of appendicectomy surgery.

Essentially, this study involves nothing from the participants themselves at all, only a retrospective review of their surgery admission. A report of the study will be sent to a medical journal approximately 4 months following completion of data analysis, and due to patient anonymity, they will not be informed of the outcomes of the project.

### Criteria

Inclusion criteria:(i)All patients who undergo an appendicectomy during the study period.(ii)Age 16 years or older at time of presentation

Exclusion criteria:(i)Previous appendicectomy or right hemi-colectomy or total colectomy.(ii)Current pregnancy at time of presentation

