## Aim

The aim of this study was to determine the variation in appendicectomy surgery wait times between rural and urban areas in Western Australia after initial presentation and diagnosis at an emergency department. Within these populations, selected outcome measures will be examined by time from:Initial presentation for the presenting complaint at an emergency department to the patient being seen by a general surgery registrar or consultant.Time from patient being seen by a general surgery registrar or consultant to surgery being performed.

The reason for taking data based on the two separate time frames is that by recording time between initial emergency department presentation to the patient being seen by the general surgery registrar or consultant, it will be possible to account for those patients who are not immediately diagnosed and then go on to have a delayed diagnostic laparoscopy and appendicectomy and evaluate and measure the magnitude of outcome impacts that an increased duration of this time could produce. Furthermore, the case report forms collect data on previous presentations of the same presenting complaint within the past week to capture any *prior premature discharge from the same site on initial evaluation of presenting complaint*.

This will allow examination of the effect of both triage wait times and timing of surgery after diagnosis on perforation, operation duration, and length of stay amongst each of the subpopulations.

Additionally, it is hoped to establish the rate of negative appendicectomies in urban and rural areas in Western Australia and if necessary make suggestions preoperatively to reduce their incidence.

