##### Rate of negative appendicectomy

This is the rate of appendicectomies performed in normal appendices. This is reported on the case report forms under macroscopic and microscopic appearance, as a normal appendix or simple or complex appendicitis. This will allow us to compare the rates of negative appendicectomies between rural and metropolitan hospitals and provide us with data to examine the potential reasons behind this, outlined in the “Introduction” section.

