## Methods

This protocol adheres to the reporting recommendations relevant specifically to an observational retrospective cohort study of the Guidelines for Reporting Outcomes in Trial Protocols: The SPIRIT-Outcomes (2022), obtained via the Equator Guidelines [12]. Consultation with doctors in the field of general surgery and rural health experts from WACHS was performed in the development of this protocol to ensure that the needs of rural populations are not misrepresented.

The study design was chosen to be retrospective due to the difficulties of prospective recruitment by medical student data collectors for whom it is unrealistic to conduct a prospective study to recruit appendicitis patients due to the transient nature of placements, especially in large metro hospitals, which would likely lead to selection bias (for more details, see “Collaborative teams”). Four separate 2-week data collection periods were preferred over one asynchronous period of data collection to provide structure for the data collection into four 6-month retrospective review periods which would allow more medical students to participate in data collection in the project overall if each student is allocated one data collection period and to divide the amount of retrospective data to be reviewed into a manageable amount for each mini-team (for more details see “Collaborative teams”).

The retrospective time period which will be examined for eligible patients and from which data is collected will be over a 2-year period from January 2022 to November 2023. Appendicectomy patients will be identified from the operating room register by members of the mini-teams discussed in the “Methods” section, expected to be mainly medical student data collectors currently on placement at the relevant hospital, and then, each respective hospital’s emergency room data collection subsequently will be accessed to fill out the case report forms. The data will be collated via case report forms based on demographics and clinical findings, pre-operative investigations, and management and follow-up. Case report forms with > 95% completeness will be accepted for pooled analysis. The expected duration of retrospective data collection will be 8 months. This includes the four 2-week data collection periods.

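### The inclusion criterion admits every appendicectomy on the theatre register, although the aims concern patients who present to an emergency department

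*Protocol article*

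**What the plan says.** In the protocol article, the Criteria section has two inclusion conditions: "All patients who undergo an appendicectomy during the study period" and "Age 16 years or older at time of presentation". The two exclusions are "Previous appendicectomy or right hemi-colectomy or total colectomy" and "Current pregnancy at time of presentation".

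Methods gives the case-finding route: "Appendicectomy patients will be identified from the operating room register". The hospital's ED data are opened afterwards, to complete the case report form.

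The Aim section describes the target as "variation in appendicectomy surgery wait times between rural and urban areas in Western Australia after initial presentation and diagnosis at an emergency department". The primary outcome is counted in hours from ED presentation, and the 12 h audit standard is set for uncomplicated acute appendicitis, also from ED presentation.

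The negative rate is defined without reference to indication: "This is the rate of appendicectomies performed in normal appendices".

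**The concern.** The eligibility rule and the aims describe different populations. Read as written, the rule lets in three kinds of operation that are not emergency care for suspected appendicitis:

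- **Incidental removal** during an operation done for another reason. A normal appendix enters the numerator of the negative rate, and the main procedure adds to operation duration.
- **Elective removal.** There is no ED wait to measure, but the patient still counts in the negative rate.
- **Planned interval removal** after an earlier episode treated without surgery. The ED-to-surgery wait is either undefined or, if the earlier visit starts the clock, weeks long.

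The negative rate is meant to show how readily surgeons operate on suspected appendicitis. With these cases included, it partly reflects each hospital's planned and incidental work. Mini-teams of five collaborators at each of nine sites apply the criteria. An unwritten restriction could be applied differently from site to site, and the site defines whether a patient is rural or urban.

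**Working it through.** **1. The plan's own figure.** Sample size gives over 1600 patients from 818 claims in one year: 2 × 818 = 1636, which agrees. By site, 4 × 350 + 5 × 50 = 1400 + 250 = 1650, also close. This is a volume estimate, not a power calculation, and the point does not depend on it.

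**2. Is there a filter elsewhere?**

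- *Exclusions.* Earlier appendix or colon resection and pregnancy remove none of the three kinds of case as such.
- *ED data (Methods).* These are opened after the case is found. They are a source for the form, not a stated condition of entry.
- *Completeness.* Forms must be more than 95% complete. A case with no ED times might fail, but only as a by-product, and its gaps could count towards the rule that drops centers with more than 5% missing data points. An incidental or interval case with enough fields filled would pass.
- *Procedure code (Sample size).* One MBS item is used to estimate volume. Criteria does not make it a condition, and the document does not say whether it covers interval or incidental removals.

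**3. Effect on the negative rate.** Let *b* be the negative rate in emergency cases (21–24%, Introduction), *f* the share of planned or incidental cases, and *h* the share of those with a normal appendix. The document gives neither *f* nor *h*; both are assumed.

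Observed rate = (1 − *f*)·*b* + *f*·*h*, so the shift is *f*·(*h* − *b*).

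| *f* | *h* = 50% | *h* = 100% |
|---|---|---|
| 2% | 0.52–0.58 points | 1.52–1.58 points |
| 5% | 1.30–1.45 points | 3.80–3.95 points |
| 10% | 2.60–2.90 points | 7.60–7.90 points |

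Each range runs from *b* = 24% to *b* = 21%. Smallest: 0.02 × (0.50 − 0.24) = 0.52 points. Largest: 0.10 × (1.00 − 0.21) = 7.90 points. If *h* were below *b*, the shift would be downward.

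**4. Effect on wait time, if the earlier visit starts the clock.** Assume log-normal emergency waits with median 16 h and mean about 20.4 h, and interval cases at 6 weeks = 42 × 24 = 1008 h.

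- Mean: 0.98 × 20.4 + 0.02 × 1008 ≈ 40 h; 0.95 × 20.4 + 0.05 × 1008 ≈ 70 h; 0.90 × 20.4 + 0.10 × 1008 ≈ 119 h.
- Median (simulated): 16.0 h becomes 16.3, 16.7 and 17.6 h at 2%, 5% and 10%.

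If the earlier visit is not used, the interval case has no wait and these figures do not arise.

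**5. Effect on the rural–urban contrast.** With 1400 v 250 patients, no true difference and two-sided 5% tests, the rejection rates are as follows. The negative rate uses *b* = 22.5% and *h* = 100%; the waits are as in step 4.

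- Equal shares (5% in both groups): near 5% for the negative rate and for the Mann–Whitney test on wait.
- 5% metropolitan v 0% rural: about 24% for each.
- 10% v 0%: about 71% for the negative rate and 73% for Mann–Whitney.

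**The case against.** The best defence is that the article, read as a whole, describes an ED cohort. Age and pregnancy are both judged at presentation, the Aim and the primary outcome place that presentation in an ED, and Methods says the data come from ED records. This shows what was intended. It does not supply an entry condition, and the first inclusion criterion, as worded, overrides the intention.

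Three further objections limit the point:

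- *Interval waits.* A reader might infer that interval patients certainly enter with waits of about 1000 h. The document does not support that. Data collection and storage describes a review of the surgery admission only, and the Aim looks back one week for earlier visits to the same site. A visit six weeks earlier falls outside both, so the wait may simply be missing.
- *Means and t-tests.* A reader might point to the large shift in the mean. Data analysis reports non-normal data as medians and uses rank tests, and waits this skewed would go that way. Median waits barely move.
- *Rural–urban bias.* A reader might infer that the comparison is biased. It is biased only if the shares differ between the groups, and nothing in the document shows that they do. Even with assumed shares of 6% urban and 1% rural, *h* = 80% and *b* = 22.5%, the rates are 0.94 × 22.5 + 0.06 × 80 = 25.95% and 0.99 × 22.5 + 0.01 × 80 = 23.08%. With 1400 v 250 patients, z is about 0.96 (p about 0.34). That gap also runs against the study's hypothesis of a higher rural rate.

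A last objection concerns the remedy. The Aim deliberately keeps patients diagnosed late who go on to diagnostic laparoscopy and appendicectomy. A narrow rule could remove normal appendices taken at such operations and lower the very rate under study. This is right, and the fix has to protect those patients.

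**Conclusion.** The point holds as a mismatch between the eligibility rule and the population of the aims. It is a fixed rule that selects the wrong population, not a detail left to an analysis plan. The clearest effect is on the absolute negative rate and on operation duration, through incidental and elective removals. For the negative rate this is about 0.5 to 8 percentage points, if such cases make up 2–10% of the register and 50–100% of them have a normal appendix. Those shares are assumptions.

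For wait time, the defect is that an interval case has no settled clock start. A large distortion of the reported wait is not established. Nor is a biased rural–urban contrast: that would need unequal shares, which are possible given the different hospital sizes but undocumented. This should be fixed before the pooled analysis, but it does not by itself invalidate the comparison.

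**What to change.** Restrict the first inclusion criterion to unplanned appendicectomy, including appendicectomy at diagnostic laparoscopy for acute abdominal symptoms, in the admission that follows an ED presentation. Add an exclusion for planned interval or elective appendicectomy and for appendicectomy incidental to an operation done for another indication.

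If forms are already entered, flag these cases, leave them out of the wait-time, operation-duration, length-of-stay and negative-rate analyses, and report their number by hospital. That count would also show whether the shares differ between rural and urban sites.

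The cost is one extra field to abstract (urgency and indication) and slightly fewer patients. If the 818 yearly claims include such cases, 1636 × (1 − *f*) gives about 1603, 1554 and 1472 at assumed shares of 2%, 5% and 10%. The article does not show that the register or the ED data record indication, so check at each site that the field can be filled.

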### Data analysis

Normally distributed data will be reported as mean (standard deviation (SD)), and non-normally distributed data will be reported as median (interquartile range (IQR)). Independent *t*-tests or ANOVAs will be used for normally distributed variables, Mann–Whitney *U* and Kruskal–Wallis tests will be used for non-normally distributed continuous or ordinal variables, and chi-squared tests will be used for categorical variable comparisons. When comparing appendicectomy wait times with complication incidence during the data analysis phase, a *P* value of 0.05 will be used to determine statistical significance. There will be no interim analysis or audit planned due to the grouping of data sets over four data collection periods. As this is a retrospective observational cohort study, there are no plans to deviate from the original protocol statistical plan or study design.

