### Primary outcome measure

Wait time from presentation (hours) to diagnosis and then surgery. This is the number of hours from initial presentation at an emergency department until review by the surgical team, diagnosis, and then surgery. These parameters will be recorded on the case report forms as date and time and will be used to compare such wait times between rural and metropolitan hospitals.

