##### Hospital stay length

This is the number of days that patients will be remaining in hospital from the date of their initial presentation in the emergency department. This will provide us with further information on the complexity of the cases as well as the post operative health needs of the patients undergoing appendicectomies.

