##### Operation duration

This is the duration in hours of the appendicectomies performed in rural and metropolitan hospitals. This again will provide general information about the complexity of cases performed.

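### Every listed test compares groups, so none relates wait time in hours to operation duration or length of stay, and none estimates an effect per hour of delay.

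*Protocol article*

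**What the plan says.** The Aim section defines two intervals: presentation to surgical review, and surgical review to operation. It promises to examine the following: "effect of both triage wait times and timing of surgery after diagnosis on perforation, operation duration, and length of stay amongst each of the subpopulations". It also says the study should measure how large the consequences of a longer first interval are.

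All the quantities involved are numeric:
- Wait time: "Wait time from presentation (hours) to diagnosis and then surgery". On recording, the Primary outcome measure section says: "These parameters will be recorded on the case report forms as date and time".
- Operation duration: "This is the duration in hours of the appendicectomies performed".
- Length of stay: "This is the number of days that patients will be remaining in hospital", counted from the date of presentation to the emergency department.

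The Data analysis section lists independent t-tests or ANOVAs for normally distributed variables. For the rest, "Mann–Whitney *U* and Kruskal–Wallis tests will be used for non-normally distributed continuous or ordinal variables, and chi-squared tests will be used for categorical variable comparisons". It names no regression or correlation method. It adds that "there are no plans to deviate from the original protocol statistical plan or study design". The only wait-versus-outcome analysis it mentions specifically is wait time against complication incidence.

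**The concern.** A t-test, ANOVA, Mann–Whitney, Kruskal–Wallis or chi-squared test needs at least one grouping variable. Wait hours against operation hours, or against days of stay, has none. To use the listed tests, someone must first create groups, most naturally by banding wait time because it is the exposure.

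Three things are then at stake:
- Group tests give no change in outcome per hour of delay, which is the quantity the Aim asks for.
- The article fixes no bands for this analysis, so they could be chosen after the data are seen.
- If the relation is smooth, banding discards information. This matters most in the rural group, planned at 5 × 50 = 250 patients, where a null result could be misread as showing that delay does no harm.

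The first two do not depend on any power assumption.

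**Working it through.** **Step 1. Which questions fit the listed tests?**

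| Question | Variables | Fits with wait time left in hours? |
|---|---|---|
| Rural v urban wait time | group, numeric | Yes: t-test or Mann–Whitney |
| Wait time and perforation | numeric, yes/no | Yes: compare hours between outcome groups |
| Wait time and complications | numeric, yes/no | Yes: same |
| Wait time and operation duration | numeric, numeric | No |
| Wait time and length of stay | numeric, numeric | No |

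The mismatch is confined to the last two rows.

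**Step 2. Is a cut-point fixed?** The 12 h figure under Audit standards is a care standard for total time from presentation. The 12, 24 and 48 h figures in the Introduction report earlier studies. None is designated for this analysis, and none is set for the two separate intervals.

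**Step 3. Sample size.** The article gives no power or effect size to reproduce. Its count is consistent: 818 × 2 = 1636, and 4 × 350 + 5 × 50 = 1650, both over 1600.

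**Step 4. Power lost by banding, under stated assumptions.** Assumed: two-sided 5% (the article gives 0.05 without sidedness), a linear relation, a normal exposure on the analysis scale, and no clustering. With correlation r, the F-test noncentrality is λ = n·r²/(1 − r²). After cutting, r² is replaced by e·r², where e is the share of exposure variance lying between bands. For a median split e = 2/π = 0.637.

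Hand check with the normal approximation, using √0.637 = 0.798:
- 80% power: (1.960 + 0.842) × 0.798 = 2.236; Φ(2.236 − 1.960) = 61%.
- 90% power: (1.960 + 1.282) × 0.798 = 2.587; Φ(2.587 − 1.960) = 73%.

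Noncentral F results for N = 1650 (N = 250 agrees within about 1 point):

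| Cut | e | From 80% | From 90% |
|---|---|---|---|
| Median | 0.637 | 61% | 73% |
| 30/70 | 0.576 | 56% | 69% |
| 20/80 | 0.490 | 50% | 62% |
| Tertiles | 0.793 | 60% | 73% |
| Quartiles | 0.86 | 57% | 71% |

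The correlations giving 80% and 90% are 0.069 and 0.080 at N = 1650, and 0.175 and 0.202 at N = 250. Simulation of Spearman correlation against the rank tests the plan names gave losses of 16–17 points (median split), 15–19 (tertiles), 20–23 (30/70) and 26–31 (20/80).

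**Step 5. How far this depends on the assumptions (median split).**

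| N | r | Uncut | Split |
|---|---|---|---|
| 1650 | 0.05 | 53% | 37% |
| 1650 | 0.07 | 81% | 62% |
| 1650 | 0.10 | 98% | 90% |
| 1650 | 0.15 | >99% | >99% |
| 250 | 0.10 | 35% | 24% |
| 250 | 0.20 | 90% | 72% |
| 250 | 0.30 | 99.9% | 97% |

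If wait time is right-skewed and the effect is linear in hours, a median split loses more at 80–90% starting power: 29–31 points for an exponential exposure, and about 40 for a lognormal one with log-SD 0.8.

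If the true effect is a step at the median, the factor works the other way. The split is then efficient, and a straight-line analysis keeps only 64% of the information.

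**The case against.** The strongest reply is that nothing in the article says wait time will be categorised. The test list is one paragraph of a journal article and does not claim to be exhaustive. The no-deviation sentence may refer to a fuller plan, and a method for secondary relations is often left to such a plan. This stands against any claim that banding is certain. It does not remove the mismatch: the article prints a specific list that cannot serve a question it sets itself, so the text needs correcting whatever a fuller plan says.

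The scope is also narrow. The primary comparison, perforation and complications can all be handled with hours intact. That stands.

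A reader might infer that wait time must be cut, and that the plan therefore loses a fixed amount of power. The documents support neither. The outcome could be grouped instead, and the loss depends on an effect size, a starting power and a cut that the article does not state. The Introduction also describes threshold-like behaviour in earlier studies, under which a well-placed cut could do better than a straight line.

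A last objection concerns the remedy. Stay is counted from presentation, so it contains the wait, and regressing one on the other gives a positive slope partly by construction. This stands, and the fix below allows for it.

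**Conclusion.** The listed tests do not fit the stated aim for two secondary outcomes, operation duration and length of stay. Followed as printed, the plan must categorise one variable at an undesignated point, and it yields no effect per hour of delay. That conclusion rests on the text alone.

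The size in power is conditional: about 15 to 30 points for common cuts if the uncut analysis has 80–90% power, the relation is roughly linear and the exposure near-normal. For a median split, the range over the cases worked above runs from under 1 point (N = 1650, r of 0.15 or more) to about 40 (strong skew), and it can change sign under a true threshold. No single figure is a property of this plan. The point is worth correcting before analysis, but it does not touch the primary comparison.

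**What to change.** In the Data analysis section, state that wait time will be analysed in hours when it is related to operation duration and length of stay. Use a regression that allows for non-linearity, and report the effect of delay with a 95% CI. Spearman correlation can serve as a simple unadjusted summary. Keep bands such as 12, 24 and 48 h for descriptive tables, and keep the listed group tests for the rural–urban comparison.

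For the stay analysis only, use time from surgery to discharge as the outcome, so that the wait is not counted on both sides. Choose a method that can handle a stay of 0 days; a plain log transform cannot.

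The cost is a few sentences, slightly more analysis work and a result less simple to present than bands. Presentation and surgery times are already recorded. The discharge date is assumed to be available, since stay cannot be computed without it.

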The planned first data collection period will only record information for eligible patients receiving appendicectomy at the relevant center between January and June 2022 retrospectively to their surgeries being performed, and then, a check of the patient’s record until the 30-day postoperative interval on the same data collection source will be conducted to record any readmissions or complications.

The planned second data collection period will only record information for eligible patients receiving appendicectomy at the relevant center between June 2022 and December 2022 retrospectively to their surgeries being performed, and then, a check of the patient’s record until the 30-day postoperative interval on the same data collection source will be conducted to record any readmissions or complications.

The planned third data collection period will only record information for eligible patients receiving appendicectomy at the relevant center between January 2023 and June 2023 retrospectively to their surgeries being performed, and then, a check of the patient’s record until the 30-day postoperative interval on the same data collection source will be conducted to record any readmissions or complications.

The planned fourth data collection period will only record information for eligible patients receiving appendicectomy at the relevant center between June 2023 and November 2023 retrospectively to their surgeries being performed, and then, a check of the patient’s record until the 30-day postoperative interval on the same data collection source will be conducted to record any readmissions or complications.

For the purpose of this project, sites under WA Country Health Service (WACHS) jurisdiction will be considered rural, that is, Albany Hospital, Bunbury Hospital, Broome Health Campus, Geraldton Hospital, and Hedland Health Campus. The other sites (Royal Perth Hospital, Sir Charles Gairdner Hospital, Fiona Stanley Hospital, Armadale Health Service) will be considered urban.

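### Rural or urban status is fixed by hospital (five versus four), but the named tests assume independent patients; if hospitals differ beyond rurality, they understate the uncertainty of the rural–urban contrast

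*Protocol article*

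**What the plan says.** The exposure is set in the Methods section of the protocol article by who runs the hospital. On one side, "sites under WA Country Health Service (WACHS) jurisdiction will be considered rural", which gives five hospitals. On the other, "The other sites (Royal Perth Hospital, Sir Charles Gairdner Hospital, Fiona Stanley Hospital, Armadale Health Service) will be considered urban". No patient-level definition, such as place of residence, is used.

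Under Primary outcome measure, the recorded dates and times "will be used to compare such wait times between rural and metropolitan hospitals". The section on the rate of negative appendicectomy sets up the same contrast for that secondary outcome.

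The Data analysis section assigns tests by type of variable: independent t-tests or ANOVA for normally distributed variables; Mann–Whitney for non-normal comparisons of two groups; and "Kruskal–Wallis tests will be used for non-normally distributed continuous or ordinal variables, and chi-squared tests will be used for categorical variable comparisons". It names no model, standard error or summary that allows for hospital, and it adds that no departure from the statistical plan is intended. The only significance level, 0.05, is written for comparing wait times with complication incidence.

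The Sample size section states that "There are over 1600 participants that are planned to be included". For the four metropolitan sites "there will be 350 participants each", and for the five rural sites "there will be 50 participants each".

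**The concern.** Patients in one hospital share its theatre access, imaging and surgical staffing. The Introduction itself explains possible rural–urban differences by features of the setting: operating thresholds, access to care and access to CT. Outcomes within a hospital are therefore likely to be correlated. Exposure does not vary within a hospital, so patients there cannot separate a rural effect from that hospital's own habits. The information on rurality comes from five hospitals against four, while the named tests count about 1650 independent patients.

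The point estimate need not be biased by this. What suffers is the stated precision: standard errors would be too small and P values too extreme for the primary outcome and for negative appendicectomy. This is a stated method that does not fit the stated design, so it is not a detail the article has left to a fuller plan.

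The point concerns the rural–urban contrasts only. Wait time varies between patients within a hospital, so comparing it with complications raises a different question.

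**Working it through.** **Inputs from the article**
- Urban: 4 hospitals × 350 = 1400 patients. Rural: 5 × 50 = 250. Total 1650.
- The article's own basis is "818 WA claims for MBS item number 30720" over one year, doubled: 2 × 818 = 1636. Both totals agree with the stated figure of over 1600. It is a volume estimate; no power, effect size or ICC is given.

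**Assumptions**
- ICC (ρ): not in the article, shown over a range.
- Two-sided 5% test for the rural–urban contrast: conventional, not stated.

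**Step 1: variance the planned tests assume** (total variance 1)

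1/1400 + 1/250 = 0.000714 + 0.004000 = 0.004714, a standard error of 0.069 SD.

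**Step 2: variance with hospital effects**

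(1 + 349ρ)/1400 + (1 + 49ρ)/250

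At ρ = 0.01: 4.49/1400 + 1.49/250 = 0.003207 + 0.005960 = 0.009167.

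**Step 3: inflation and actual error rate**

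Inflation D = step 2 / step 1. At ρ = 0.01: 0.009167/0.004714 = 1.945.

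Actual error = 2 × [1 − Φ(1.96/√D)]. At ρ = 0.01: 1.96/√1.945 = 1.405, which gives 16.0%.

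| Assumed ICC | Inflation D | Actual error, formula | Simulated t / Mann–Whitney / chi-squared | Simulated t-test on nine hospital means |
|---|---|---|---|---|
| 0 | 1.00 | 5.0% | 4.5 / 4.5 / 5.5% | 4.0% |
| 0.001 | 1.09 | 6.1% | – | – |
| 0.005 | 1.47 | 10.6% | – | – |
| 0.01 | 1.94 | 16.0% | 16.3 / 15.9 / 15.7% | 4.6% |
| 0.02 | 2.89 | 24.9% | 25.3 / 24.3 / 25.2% | 4.8% |
| 0.05 | 5.72 | 41.3% | 42.7 / 41.9 / 41.5% | 5.2% |

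The simulations used 4000 runs per ICC, the planned hospital sizes and no true rural–urban difference. The chi-squared column used a 22% event rate, chosen from within the 21–24% negative appendicectomy rate in the Introduction. All three patient-level tests behave alike. The t-test on nine hospital means has 9 − 2 = 7 degrees of freedom and stays close to 5% even with hospital sizes of 350 and 50.

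**Step 4: one unusual hospital**

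If one of the five equal-sized rural hospitals is shifted by 0.7 SD, the rural mean moves by 0.7/5 = 0.14 SD. Against the standard error in step 1, z = 0.14/0.0687 = 2.04. That is nominally significant with no general rural effect.

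**The case against.** The strongest reply is that the nine hospitals need not be seen as a sample. The article doubles statewide claims to 1636 and allocates 1650 patients to these sites, so its own figures treat them as roughly the whole Western Australian volume. Part of the Aim is descriptive. If the target were only the patients treated at these hospitals, a pooled patient-level comparison would be a defensible description. That much stands. It does not rescue the plan, because the Introduction puts forward a hypothesis about rural hospitals and its causes, and the Aim speaks of rural and urban areas across the state. Reading the difference as one of rurality needs allowance for hospital.

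A second reply is that ANOVA and Kruskal–Wallis are listed and the Abstract speaks of comparing negative rates between hospitals, so an outlying site might be noticed. That also stands, but a test across nine sites shows only that hospitals differ. It gives no valid test of rural against urban.

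A reader might infer that the error rate certainly fails, or that hospital differences have been shown. The documents support neither: they give no ICC, and at zero the patient-level tests hold their level. The Introduction cites an audit with a 45.58% negative rate at Bunbury, a study site, but that audit was pediatric and this study enrols patients aged 16 or older. It illustrates that a site can be atypical and measures nothing here.

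**Conclusion.** The concern holds in conditional form. If hospitals differ at all beyond rurality (ICC above 0), the named tests understate the uncertainty of the rural–urban contrast for the primary outcome and for negative appendicectomy. At the planned sizes, an assumed ICC of 0.005 roughly doubles a conventional 5% error rate to about 11%. The range from ICC 0.001 to 0.05 runs from about 6% to about 41%.

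This rests on three assumptions: a non-zero ICC, a conventional two-sided 5% level, and a conclusion about rural and urban care in general. A reader might infer that the plan breaks a 5% level it set for this contrast. It set none there; its 0.05 is written for wait time against complications.

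A reader might also want a single effective sample size. The figure depends on its definition: at ICC 0.01, 1650/1.945 is about 848 if the 1400:250 split is kept, but the two groups separately give 1400/4.49 + 250/1.49 = 312 + 168 = 480. The error rate is the clearer measure.

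Because the mismatch affects the primary aim and can be corrected cheaply before analysis, it should be corrected.

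**What to change.** For each rural–urban contrast, replace the patient-level test with one hospital-aware primary analysis. Either of these would do:
- a t-test on hospital-level means (wait time, on the log scale if skewed) or proportions (negative appendicectomy), with degrees of freedom equal to the number of hospitals minus two; or
- for log wait time, a linear mixed model with a random hospital intercept and small-sample degrees of freedom (Kenward–Roger or Satterthwaite).

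With nine sites there are about 7 degrees of freedom, and fewer if the missing-data rule in Methods excludes centers. The small-sample corrections do not carry over routinely to a logistic mixed model, so the hospital-level t-test is the simpler choice for binary outcomes. Ordinary cluster-robust standard errors are unreliable with nine clusters. A permutation test over hospital labels is not exact when hospital sizes differ by group (350 against 50).

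State the significance level and sidedness for this contrast, and report hospital-specific results beside the pooled one. If only patient-level tests are kept, limit the conclusion to a description of these nine hospitals.

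The cost is wider confidence intervals and slightly more analysis work. No new data should be needed: the case report form is not shown, but assigning rural status and excluding centers both require the hospital to be known.
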